## Abstract

**Background:**

Binge eating disorder is a prevalent adolescent disorder, associated with increased eating disorder and general psychopathology as well as an increased risk for overweight and obesity. As opposed to binge eating disorder in adults, there is a lack of validated psychological treatments for this condition in adolescents. The goal of this research project is therefore to determine the efficacy of age-adapted cognitive-behavioral therapy in adolescents with binge eating disorder – the gold standard treatment for adults with binge eating disorder.

**Methods/design:**

In a single-center efficacy trial, 60 12- to 20-year-old adolescents meeting diagnostic criteria of binge eating disorder (full-syndrome or subthreshold) according to the Diagnostic and Statistical Manual of Mental Disorders 4^th^ or 5^th^ Edition, will be centrally randomized to 4 months of cognitive-behavioral therapy (n = 30) or a waiting-list control condition (n = 30). Using an observer-blind design, patients are assessed at baseline, mid-treatment, post-treatment, and at 6- and 12-month follow-ups after the end of treatment. In 20 individual outpatient sessions, cognitive-behavioral therapy for adolescents focuses on eating behavior, body image, and stress; parents receive psychoeducation on these topics. Primary endpoint is the number of episodes with binge eating over the previous 28 days at post-treatment using a state-of-the art clinical interview. Secondary outcome measures address the specific eating disorder psychopathology, general psychopathology, mental comorbidity, self-esteem, quality of life, and body weight.

**Discussion:**

This trial will allow us to determine the short- and long-term efficacy of cognitive-behavioral therapy in adolescent binge eating disorder, to determine cost-effectiveness, and to identify predictors of treatment outcome. Evidence will be gathered regarding whether this treatment will help to prevent excessive weight gain. If efficacy can be demonstrated, the results from this trial will enhance availability of evidence-based treatment of adolescent binge eating disorder.

**Trial registration:**

German Clinical Trials Register: DRKS00000542

## Background

Binge eating disorder (BED), a provisional category in the Diagnostic and Statistical Manual of Mental Disorders Fourth Edition (DSM-IV-TR) [1], was approved in the fifth revision DSM-5 [2] as its own diagnostic category of eating disorder. BED is characterized by recurrent binge eating that occurs, in contrast to the binge eating in bulimia nervosa (BN), in the absence of regular inappropriate compensatory behavior to prevent weight gain (e.g., self-induced vomiting). BED has been identified in 1.6% of 13- to 18-year-old adolescents from the community [3], and in up to 25% of treatment-seeking adolescents [4,5]. However, it is still debated as to whether the DSM diagnostic criteria adequately capture the presentation of BED in children and adolescents. For example, beyond objective binge eating as defined in the DSM criteria of BED (i.e., loss of control over eating a significantly large amount of food) [2], a substantial proportion of adolescents report subjective binge eating that is not part of the DSM diagnostic criteria of BED (i.e., loss of control over eating a subjectively large amount of food), but is psychopathologically relevant [4,6] (both types of binge eating are hereafter referred to as binge eating). In addition, lowered diagnostic thresholds have been proposed for the diagnosis of BED in youth [7,8]. Subthreshold BED was found to be associated with marked impairment and increased risk of developing a full-syndrome presentation over time [9].

Similar to BED in adults, this disorder in adolescence is associated with increased eating disorder psychopathology (e.g., weight concern) and general psychopathology (e.g., depression, anxiety), impaired quality of life, and overweight and obesity [4,10,11]. BED and its associated eating disorder and general psychopathology were found to be longitudinally predicted by binge eating in youth [12-14]. As postulated by maintenance theories of binge eating developed for adults [15,16] and validated for youth [17], binge eating in youth may be maintained through negative affect and difficulties in regulating these mood states [18-20]. Weight-related teasing and a negative body image were closely linked with greater binge eating in youth [21-23]. Further, binge eating emerges in the context of increased impulsivity, irregular meal patterns, and interpersonal problems such as dysfunctional family interactions [24-27]. These results suggest that patterns of non-normative eating behavior, difficulties in regulating negative emotional states, a negative body image, and interpersonal problems are important targets of intervention.

Of great concern are findings that youth with binge eating or BED show increased weight gain and obesity onset over time [14,28-31]. Given the psychological, social, and medical sequelae of obesity [32,33], the risk of tracking the excess body fat and comorbidities into adulthood [34,35], and the associated health-care costs [36], it is of the highest relevance to develop efficacious interventions for the treatment of BED in adolescents to alleviate this disorder’s symptomatology and to prevent excessive weight gain.

Related to the recency of research about BED in adolescence, there is a lack of validated treatments for this age group. For adults with BED, cognitive-behavioral therapy (CBT) is the most well-established psychological treatment, as reflected in systematic reviews [37-39], meta-analysis [40], and clinical guidelines [41], although superiority to other bona fide treatments has not been demonstrated clearly [42]. Efficacy studies of CBT documented substantial reductions in binge eating and associated symptomatology that can be maintained over the long-term [43]. There is also evidence that patients who achieve abstinence from binge eating lose a small but significant amount of weight when compared to those who remain symptomatic [44,45].

Among the few studies evaluating CBT or other psychological treatments for adolescents with recurrent binge eating, CBT was in a pilot randomized-controlled trial (RCT) compared with a delayed treatment control condition. This CBT trial was efficacious in yielding abstinence from recurrent binge eating over a three-month follow-up in 12- to 18-year-old adolescents (n = 26) [46]. In addition, concerns about shape, weight, and eating were significantly reduced. The age-adapted CBT manual comprised eight individual sessions over 3 months on nutritional management, weight control, and body image, and up to four optional sessions on food and mood and interpersonal relationships. Another study focused on an Internet-based mode of treatment delivery: a 16-week Internet-based intervention program using CBT-principles (among other principles) was part of a waiting-list (WL) controlled randomized study. The Internet program was found to be efficacious in facilitating weight loss or weight maintenance, and reducing recurrent binge eating and shape and weight concerns, in overweight adolescents over a 5-month follow-up period (n = 105) [47]. In addition, a small-scale (n = 38) randomized-controlled pilot study demonstrated feasibility of 12-week group interpersonal psychotherapy in 12- to 17-year-old adolescent girls at risk for overweight, with about half of the patients suffering from binge eating [48]. The results also suggested that interpersonal psychotherapy reduced binge eating at 3-month follow-up and led to better weight maintenance than a standard health education group at 9-month follow-up. Further evidence is available on CBT or CBT-based guided self-help for adolescents with BN or with mixed eating disorder diagnoses [49,50], providing support for CBT-based treatment in the related eating disorder of adolescent BN. Thus far, however, confirmatory evidence on the efficacy of psychological treatments for BED in adolescents is lacking, moderators and mediators are unknown, and cost-effectiveness has not been evaluated.

In this context, the aim of the Binge Eating Disorder in Adolescents (BEDA) study is to adapt an established CBT manual for adult BED to adolescent BED, and evaluate its short- and long-term efficacy, relative to a WL control condition in a single-center randomized trial. Additional objectives are to identify outcome predictors (moderators and mediators) and to evaluate cost-effectiveness.

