### Design, participants, and procedures

#### Study design

BEDA is a single-center, prospective, randomized superiority trial, evaluating the efficacy and cost-effectiveness of CBT (experimental condition) compared to a WL control condition. The study design is depicted in Figure 1. The study period lasts 4 months per patient in the experimental condition (4 months of CBT) and 8 months in the control condition, including 4 months of WL and 4 months of CBT; each patient is offered individual CBT. Using an observer-blind design, patients are assessed at baseline, 2 months after randomization (mid-CBT; mid-WL), 4 months after randomization (post-CBT; post-WL or pre-CBT/WL), and at 6- and 12-months follow-up after the end of treatment (6-fu CBT, 12-fu CBT; 6-fu CBT/WL, 12-fu CBT/WL). The patients in the WL condition are assessed additionally 2 months (mid-CBT/WL) and 4 months (post-CBT/WL) after the end of the waiting period (i.e., after post-WL or pre-CBT/WL).

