### Procedures

Adolescents are screened by telephone for eligibility in the study. Eligible adolescents and at least one parent are invited to the IFB Outpatient Unit for a diagnostic visit. At the outset of this visit, informed consent is gathered in a written format as described. At baseline assessment, inclusion and exclusion criteria are evaluated using the clinical interviews described below. Additionally, sociodemographic, anamnestic, anthropometric, and clinical data, and health economic parameters, are obtained using interviews, self-report-questionnaires, and objective measurement as described below. After baseline assessment, included patients are centrally randomized into the CBT or WL arm. Following randomization into the CBT arm, patients are offered treatment over 4 months. Following randomization into the WL arm, patients are invited to CBT over 4 months, after a waiting-list period of 4 months.

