#### Control intervention – waiting list (WL)

Half of the patients will be randomly assigned to a WL control condition. All WL patients are guaranteed individual CBT after a waiting period of 4 months (equal to the duration of CBT). The WL patients are instructed not to seek any other medical or psychological treatment for BED or obesity during the WL period without informing the project leader.

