### Measures

#### Primary and secondary outcomes

The primary outcome measure is the number of binge eating episodes over the previous 28 days 4 months after randomization (post-CBT, post-WL), which is a standard measure within treatment trials of adult BED [40]. The number of binge eating episodes is assessed with the German version of the Eating Disorder Examination (EDE) [58-60], a validated semi-structured interview regarded as the gold standard for the diagnosis and psychopathological assessment of eating disorders. If necessary, age-adapted language is used from the child version of the EDE [61,62]. For adult BED, it is common to determine the difference in the number of episodes or days with objective binge eating between baseline and follow-up and test for a difference between a treatment and control group [40]. In adolescents, this measure has severe disadvantages since the large variance in the number of episodes with binge eating (i.e., objective and objective binge eating [47,48]) can result in imbalances between randomized arms (e.g., [47]). Abstinence rates, another typical measure in treatment trials for adult BED [40], have the disadvantage that patients who reduce their binge eating substantially, but not completely, are treated as failures. Hence, we chose to consider the ratio of the number of binge eating episodes at 4 months after randomization to the number at baseline as primary outcome criterion.

Secondary outcome measures include the number of binge eating episodes 2 months after randomization (mid-CBT, mid-WL), and maintenance of treatment success regarding the number of binge eating episodes at 6 and 12 months following CBT (6-fu CBT, 12-fu CBT). Additional secondary outcomes are also measured at 2 and 4 months after randomization and at 6 and 12 months following CBT: the number of days with binge eating; abstinence (i.e., zero binge eating episodes) from binge eating; eating disorder psychopathology (all determined through the EDE); additional aspects of non-normative eating behavior as determined through the Dutch Eating Behavior Questionnaire [63,64]; the severity of depressive symptoms [65,66]; self-esteem [67,68]; quality of life [69,70], and body mass index (BMI, kg/m^2^). Body weight and height is objectively measured through calibrated instruments. Psychiatric comorbidity is determined per structured clinical interview K-DIPS [71] 6 and 12 months following CBT.

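### The aim of long-term efficacy relative to waiting list cannot be met, because the comparison with untreated patients ends at month 4

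*Protocol article*

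**What the plan says.** The Background gives the aim as to "evaluate its short- and long-term efficacy, relative to a WL control condition in a single-center randomized trial". The Discussion paragraph of the Abstract repeats the long-term part without naming the comparator: "This trial will allow us to determine the short- and long-term efficacy of cognitive-behavioral therapy in adolescent binge eating disorder". It adds on weight: "Evidence will be gathered regarding whether this treatment will help to prevent excessive weight gain". The main Discussion section returns to both themes: a confirmatory comparison with WL followed up for one year, and evidence on excessive weight gain.

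The sections on conduct limit the waiting period. Under Study design, the study period is "8 months in the control condition, including 4 months of WL and 4 months of CBT; each patient is offered individual CBT". Procedures states: "Following randomization into the WL arm, patients are invited to CBT over 4 months, after a waiting-list period of 4 months". The section on the control intervention states: "All WL patients are guaranteed individual CBT after a waiting period of 4 months (equal to the duration of CBT". Study design places the 6- and 12-month follow-ups after the end of treatment in each arm. WL patients have two extra visits, 2 and 4 months after their wait ends.

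Under Primary and secondary outcomes, most secondary outcomes, BMI among them, are measured at months 2 and 4 and again 6 and 12 months after CBT. Comorbidity differs: "Psychiatric comorbidity is determined per structured clinical interview K-DIPS [71] 6 and 12 months following CBT". The cost questionnaire is given at every assessment.

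Hypothesis 1 sets superiority over WL at 4 months. Hypothesis 2 and the Data analytic plan treat the later visits as maintenance of gains.

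**The concern.** An efficacy claim relative to WL needs a group that is still waiting when the outcome is measured. In this design no such group is planned after month 4. The aim nevertheless extends the claim to the long term and attaches it to the randomised comparison.

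After month 4, change from baseline in patients who have been offered CBT mixes any treatment effect with spontaneous remission, regression to the mean and, for weight, growth. Regression to the mean is to be expected because patients are selected for current binge eating. If results at 6 and 12 months are presented under the aim as worded, readers may take them as randomised evidence of lasting efficacy, or of lasting prevention of weight gain.

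**Working it through.** **1. The plan's own figures.** Power analysis: 27 per group with 10% dropout gives 27 / (1 − 0.10) = 30 per arm and 2 × 30 = 60 in total, as stated. Study design: the control condition lasts 4 + 4 = 8 months, as stated. The 95% power comes from a simulation whose inputs the article does not give. Nothing here depends on it.

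**2. Visits in months since randomisation** (from Study design).

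| Visit | CBT arm | WL arm |
|---|---|---|
| Baseline | 0 | 0 |
| Mid-CBT / mid-WL | 2 | 2 |
| Post-CBT / post-WL | 4 | 4 |
| Mid-CBT in WL arm | – | 4 + 2 = 6 |
| Post-CBT in WL arm | – | 4 + 4 = 8 |
| 6-month follow-up | 4 + 6 = 10 | 8 + 6 = 14 |
| 12-month follow-up | 4 + 12 = 16 | 8 + 12 = 20 |

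The arms share visits at 0, 2 and 4 only. The last visit of an untreated WL patient under the plan is at month 4. The CBT arm's visits at months 10 and 16 have no WL visit at the same time, and by then the WL arm has been offered CBT. The period with an untreated comparator is 4 of 16 months in the CBT arm and 4 of 20 in the WL arm.

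**3. What this leaves for each outcome.**

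| Outcome | Randomised contrast with untreated WL | After month 4 |
|---|---|---|
| Binge eating and most secondary outcomes, including BMI | Months 2 and 4 | None |
| Costs | Up to month 4 | None |
| Comorbidity (K-DIPS) as an outcome | None | None; measured only 6 and 12 months after CBT |

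**4. Growth and later BMI.** The documents give no rate at which BMI rises with age. Assume 0.2 to 0.8 kg/m² a year. By month 16 this is 0.2 × 16/12 = 0.27 to 0.8 × 16/12 = 1.07 kg/m². By month 4 it is 0.2 × 4/12 = 0.07 to 0.8 × 4/12 = 0.27 kg/m², and there it is expected to affect both randomised arms alike. Growth is therefore a difficulty for the uncontrolled follow-up and hardly one for the month-4 contrast.

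**5. Adding the WL arm's post-CBT follow-up to the maintenance models.** The sample could rise from 30 to at most 60, and intervals would narrow by 1 − 1/√2 = 0.29, or 29%. This is a best case: all WL patients would have to start CBT and be retained as well as the CBT arm.

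**The case against.** The strongest reply is that the operative text is already narrower than the aim. Hypothesis 1 tests superiority over WL at 4 months, hypothesis 2 and the Data analytic plan speak of maintenance, secondary outcomes are exploratory, and no section specifies a test of CBT against WL after month 4. The Abstract's sentence on long-term efficacy does not mention WL, and its sentence on weight is hedged. All of this stands, and it makes the matter one of the stated aim and claims rather than of the tests. It does not remove the fault: the aim is explicit, nothing qualifies it, and no analysis plan can supply an untreated group after month 4.

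Several stronger readings are tempting, and the documents do not support them.

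- A reader might infer that every WL patient starts CBT at month 4. The text says that they are guaranteed and invited to it. The conclusion is the same, since any who decline would be self-selected and not a randomised control.
- A reader might infer that no randomised comparison of any kind remains. Immediate versus delayed CBT is still a comparison of randomised groups. It answers a different question from efficacy versus no treatment.
- A reader might infer that weight and costs have no controlled result. Both do, up to month 4. No section commits to a longer cost horizon against WL.
- A reader might infer that the WL arm's follow-up data will go unused. Only the sentence on binge-eating episodes carries labels for the CBT arm alone, and the maintenance models are not restricted to one arm.
- A reader might infer that BMI will be analysed only in raw units. The article names the measure and its unit and fixes no analysis scale.
- Comorbidity is not in hypothesis 2's list of superiority claims, so no stated hypothesis about it fails.

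**Conclusion.** The aim is wrong as written. The design supports efficacy relative to untreated WL at months 2 and 4 and not beyond. Comorbidity as an outcome has no such comparison at any time. This follows from the visit schedule and the guarantee of CBT alone, and needs no numerical assumption.

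The weight claim against WL is likewise limited to 4 months. Later BMI in 12- to 20-year-olds is uncontrolled and subject to growth. The direction of that concern is clear, but its size, about 0.3 to 1.1 kg/m² by month 16, rests entirely on the assumed yearly rise.

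The month-4 primary analysis, its inference and the sample size are unaffected. Offering CBT to waiting patients is a legitimate design choice and is not criticised here; the fault lies in the claim.

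**What to change.** 1. Restate the aim in the Background, and the matching sentences in the Abstract and Discussion, as efficacy versus WL up to 4 months after randomisation. State that cost-effectiveness and BMI or weight-gain effects versus WL are confined to the same period.
2. Describe the 6- and 12-month data, including K-DIPS comorbidity, as maintenance or course after CBT without an untreated control, in line with hypothesis 2 and the Data analytic plan. Make no claim of long-term efficacy, or of long-term prevention of weight gain, versus WL.
3. Report an age- and sex-standardised BMI alongside raw kg/m².
4. Optionally, state whether the WL arm's post-CBT follow-up enters the maintenance models. Pooling the arms treats immediate and delayed CBT as interchangeable, which would need justification, so it is a choice and not a requirement.

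The cost is wording, less favourable long-term claims, and the choice of a BMI reference that covers the oldest patients. No new data or visits are needed. The article says that post-treatment data are released only after the 12-month follow-up is complete, so the claims can be restated before results are known.

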## Methods/design

### Hypotheses

(1) Age-adapted individual CBT will be superior to WL in reducing the number of binge eating episodes in adolescents with BED 4 months following randomization.

(2) Age-adapted individual CBT will be superior to WL in reducing the number of days with binge eating episodes; leading to greater abstinence from binge eating; reducing eating disorder psychopathology and the severity of depressive symptoms; increasing self-esteem and quality of life; and stabilizing body mass index. The therapeutic gains will occur at mid-treatment and will be maintained at 6 and 12 months following CBT.

(3) Age adapted individual CBT will be cost-effective.

### Design, participants, and procedures

#### Study design

BEDA is a single-center, prospective, randomized superiority trial, evaluating the efficacy and cost-effectiveness of CBT (experimental condition) compared to a WL control condition. The study design is depicted in Figure 1. The study period lasts 4 months per patient in the experimental condition (4 months of CBT) and 8 months in the control condition, including 4 months of WL and 4 months of CBT; each patient is offered individual CBT. Using an observer-blind design, patients are assessed at baseline, 2 months after randomization (mid-CBT; mid-WL), 4 months after randomization (post-CBT; post-WL or pre-CBT/WL), and at 6- and 12-months follow-up after the end of treatment (6-fu CBT, 12-fu CBT; 6-fu CBT/WL, 12-fu CBT/WL). The patients in the WL condition are assessed additionally 2 months (mid-CBT/WL) and 4 months (post-CBT/WL) after the end of the waiting period (i.e., after post-WL or pre-CBT/WL).

**Figure 1 F1:**
[figure not shown]
Study design.

### Participants

A total of 60 12- to 20-year-old adolescents meeting age-adapted DSM criteria of BED will be randomized to either CBT (n = 30) or WL (n = 30). Inclusion criteria are summarized below. Based on the evidence on classification of BED in youth (see Introduction), age-adapted diagnostic criteria of BED are used in order to determine: BED according to DSM-IV-TR based on objective and/or subjective episodes of binge eating *or* BED according to DSM-5 based on objective and/or subjective episodes of binge eating *or* Subthreshold BED according to DSM-5. To ensure generalization of study results, exclusion criteria are kept to a minimum.

